### 2.6. Data Collection Methods

Data will be collected at five time points: during the screening visit, at hospital admission, at hospital discharge, at 30 days after surgery (by telephone), and 90 days after surgery.

Screening visit. The screening visit takes place during the pre-admission visit by the referring dietitian/nutritional biologist, usually 14–28 days before surgery. After evaluation of the inclusion and exclusion criteria and signing of informed consent, the following data will be collected: demographics; medical history and medications; laboratory data; pregnancy test in women of childbearing potential; anthropometric parameters; nutritional risk according to NRS-2002; body composition via analysis of basal CT scan images (if performed in the two months prior to the preadmission visit); muscular strength by digital hand-grip dynamometer and sit-and-stand test.Hospital admission. Hospital admission is usually the day before surgery. The following data will be recorded: anthropometric parameters; muscular strength as described above; compliance based on the number of servings of supplements consumed by the patient; tolerability measured using a questionnaire.Hospital discharge. Hospital discharge is usually 15 to 20 days after surgery. The following data will be recorded: anthropometric parameters; muscle strength as above; type of urinary reconstruction; day of recovery of bowel function; day of discontinuation of systemic/peridural opioid analgesic therapy, if any; day of removal of naso-gastric tube, if any; use of parenteral nutrition and/or ONS after surgery; blood transfusions performed during hospital stay; need for ICU stay; vital status.Thirty days after surgery. A follow-up telephone call will be made 30 days after surgery. The following data will be collected, if available: postoperative complications and other medical conditions; re-hospitalisation; vital status. If patients are still hospitalised 30 days after surgery, data will be collected during hospitalisation.Ninety days after surgery. A follow-up visit will be performed ninety days after surgery. The following data will be collected, if available: anthropometric parameters; postoperative complications and other medical conditions; re-hospitalisation; initiation of adjuvant chemotherapy; vital status. If patients are still hospitalised 90 days after surgery, data will be collected during hospitalisation.

### 2.7. Data Management and Statistical Analysis

#### 2.7.1. Determination of Sample Size

Sample size calculations are based on the primary endpoint. We estimate an expected absolute reduction of 17% in the complication rate or patients receiving preoperative IMN compared to patients receiving preoperative standard ONS. Postoperative complications following RC are known to occur in approximately 64–70% of patients without nutritional supplementation [4,18]. A small randomised pilot study showed a 30-day complication rate of around 73% in patients receiving standard ONS [19]. Data on patients receiving IMN are heterogeneous, due to high variability in IMN dosage and description of outcomes in the literature. The clinical studies evaluating the impact of IMN on patients undergoing RC report 30-day complication rates of 40% [20], 63% [21], 55.4% [22], and 71% [19]. In this study, we estimated an expected complication rate of 72% in the standard ONS group and 55% in the IMN group. The expected complication rate in the standard ONS group was derived from a previous study that enrolled only males and provided both pre- and postoperative standard ONS supplementation [19], while the estimation of the complication rate in the intervention group was derived from clinical studies on IMN [19,20,21,22].

Using the expected complication rates, a sample size calculation was performed (80% power, and a two-sided type I error = 0.05); a minimum 125-patient sample size was required in each group. The number of subjects was increased up to 130 in each group to take into account a potential drop-out rate of 4%. Therefore, the total number of patients enrolled for the entire study (all sites combined) will be 260. Based on the expected accrual rate, the study duration will take place over 30 months.

#### 2.7.2. Planned Analyses

The main analysis will be conducted according to the intention-to-treat (ITT) principle: patients in the analysis set will be analysed according to the treatment to which they were randomised, regardless of the treatment actually received. The ITT population will be used for the primary and secondary endpoints. Per-protocol (PP) analyses will also be performed, taking into account the treatment actually received. Specifically, per-protocol analyses will compare compliant patients in the IMN group with compliant patients in the control group for the primary and key secondary endpoints. The safety population will include all patients who consume at least one dose of the assigned treatment and will be used for the safety analyses. The two-sided type I error will be set at 5% (adjusting for Bonferroni’s correction when necessary). All statistical analyses will be performed using Stata 18 (StataCorp. 2021. Stata Statistical Software: Release 18. College Station, TX, USA: StataCorp LLC.)

The primary objective will be analysed using a binomial regression model, with link identity. The risk difference and its 95% confidence interval (95%CI) will be derived from the model. Huber–White robust standard errors will be used while clustering on centre to account for the lack of independence within centre.

The statistical analysis for the key secondary objective and for several other secondary objectives (no. 9, 13, and 14) will be performed in the same way as the primary objective. Other secondary objectives will be analysed using a time-to-event analysis (no. 1–5 and 10–12) or with Mann–Whitney U test (no. 6–8). Effect modification by subgroup will be assessed by introducing the interaction of subgroup and treatment in the corresponding statistical model (no. 15).

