### 2.4. Nutritional Interventions

The study intervention consists of the preoperative administration of a high-calorie, high-protein, immunonutrient-enriched ONS (Impact^®^ Oral (237 mL per dose); Nestlé Health Science—Creully Sur Seulles—France). Two doses of Impact^®^ Oral per day will be given from 7 days before surgery until the day before RC. Specifically, this formula is enriched in immunonutrients (arginine, RNA nucleotides and omega-3 fatty acids) and provides 36 g of protein and 682 kcal/day at the proposed therapeutic dose.

Patients in the control group will receive a high-calorie, high-protein liquid ONS (Meritene^®^ Protein Drink (200 mL per serving); Nestlé Health Science—Creully Sur Seulles—France). Two doses of Meritene^®^ Protein Drink per day will be given from 7 days before surgery until the day before RC. Specifically, this formula provides 38 g of protein and 500 kcal/day at the proposed therapeutic volume.

In the event of unplanned delays in the surgical procedure, the 7-day administration of IMN/ONS will be temporarily interrupted and then resumed, with the last dose taken the day before surgery (e.g., if surgery is delayed after a patient has already taken 5 doses of IMN/ONS, he/she will take the remaining 9 doses in the 5 days before the new surgery date).

To improve compliance, nutritional counselling will be provided at the pre-admission visit in both treatment arms. Patients will be advised on how to take the supplements (i.e., they will be instructed to drink the supplements very slowly between meals) and will be given an information leaflet on how to take the supplements. Overweight and obese patients will be given dietary advice on how to reduce caloric intake to avoid an excessive increase in daily caloric intake. Patients will be asked to return any unused product on admission to the hospital in order to quantify the amount of product consumed.

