The key secondary objective is to compare preoperative IMN with standard ONS in terms of the rate of severe complications (i.e., Clavien–Dindo grade ≥ III) in the first 30 days after RC. The other secondary objectives of the study are as follows:To compare preoperative IMN with standard ONS in terms of the rate of severe complications in the first 90 days after RC;To compare preoperative IMN with standard ONS in terms of the rate of infectious complications in the first 30 and 90 days after RC;To compare preoperative IMN with standard ONS in terms of the rate of occurrence of other medical conditions in the first 30 and 90 days after RC;To compare preoperative IMN with standard ONS in terms of time to recovery of bowel function, defined as the time from surgery to first flatus;To compare preoperative IMN with standard ONS in terms of time to postoperative mobilization, defined as the time from surgery to first walk;To compare preoperative IMN with standard ONS in terms of changes in muscle strength, defined as the difference in hand-grip strength (mean of three consecutive measurements from the dominant hand) and in the sit-and-stand test from the preadmission visit to the day before surgery to hospital discharge;To compare preoperative IMN with standard ONS in terms of weight modifications, defined as the difference in body weight from the preadmission visit to the day before surgery to hospital discharge to the 90-day follow-up visit;To compare preoperative IMN with standard ONS in terms of biochemical nutritional index modifications, i.e., changes in haemoglobin, lymphocytes, albumin, prealbumin, C-reactive protein, cholinesterase, total cholesterol, glucose, and creatinine, from the preadmission visit to the day before surgery to hospital discharge;To compare preoperative IMN with standard ONS in terms of the need for blood transfusions, defined as the percentage of patients who receive blood transfusions during their hospital stay;To compare preoperative IMN with standard ONS in terms of length of stay (LOS), defined as the time from hospital admission to discharge at home or to another facility;To compare preoperative IMN with standard ONS in terms of 30-day and 90-day readmission rate, defined as the incidence of unplanned re-hospitalization due to all causes in the first 30 and 90 days;To compare preoperative IMN with standard ONS in terms of 30-day and 90-day mortality, defined as death rate due to all causes during the first 30 and 90 days post-surgery;To compare the compliance to preoperative IMN and standard ONS, defined as the percentage of patients consuming ≥ 80% of the prescribed supplement in the 7 days before surgery;To compare the tolerability of preoperative IMN and standard ONS, defined as the percentage of patients experiencing at least one moderate–severe adverse gastrointestinal effects during the 7-day intervention period;To compare preoperative IMN with standard ONS for the primary endpoint and the key secondary endpoint in the subgroups of the following:

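### The additional per-protocol analysis compares compliers with compliers, with no adjustment described, so it may show a spurious difference of a few points; the ITT main analysis is unaffected

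*Protocol article*

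**What the plan says.** Section 2.7.2 of the Protocol article ranks the analyses: "The main analysis will be conducted according to the intention-to-treat (ITT) principle", and "The ITT population will be used for the primary and secondary endpoints". It then adds a further analysis: "Per-protocol (PP) analyses will also be performed, taking into account the treatment actually received". The method is specified: "per-protocol analyses will compare compliant patients in the IMN group with compliant patients in the control group for the primary and key secondary endpoints". No covariate adjustment or weighting is described for this contrast.

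The section does not define a compliant patient. The one threshold in the article is in Section 2.5, where compliance is "the percentage of patients consuming ≥ 80% of the prescribed supplement in the 7 days before surgery". Under Section 2.6 it is recorded at hospital admission, usually the day before surgery.

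Section 2.4 describes two different products, each taken twice a day. The IMN product (237 mL per dose) "provides 36 g of protein and 682 kcal/day at the proposed therapeutic dose" and contains arginine, nucleotides and omega-3 fatty acids. For the control product (200 mL per dose), "this formula provides 38 g of protein and 500 kcal/day at the proposed therapeutic volume". Section 2.1 states that the trial is open-label.

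**The concern.** Compliance is observed after randomisation. Restricting each arm to its compliers therefore gives up the balance that randomisation provides. This matters most when the selection can work differently in the two arms. Here that is plausible: one product is larger in volume, higher in energy and different in content, and patients know which one they have.

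Patients who do not finish an oral supplement may also be at higher surgical risk. If one product is finished less often, its compliers would be a more favourable selection than the other arm's, and the contrast would show a difference even with no treatment effect. Because this analysis is planned for the primary and key secondary endpoints, a biased result could be read as support for IMN, or as evidence against it, where ITT shows nothing.

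**Working it through.** **Plan figures used.** Section 2.7.1 assumes 72% complications with standard ONS and 55% with IMN, 80% power and two-sided 5% error. With pooled variance and no continuity correction:

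n = [1.960·√(2·0.635·0.365) + 0.842·√(0.72·0.28 + 0.55·0.45)]² / 0.17² = (1.334 + 0.564)² / 0.0289 ≈ 125 per arm.

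This reproduces the stated 125. Planned enrolment is 130 per arm. The plan gives no figure for compliance by arm or for risk in non-compliers, so those inputs below are assumptions.

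**Product differences (Section 2.4).**
- Volume: 2 × 237 = 474 mL/day versus 2 × 200 = 400 mL/day (+18.5%).
- Energy: 682 versus 500 kcal/day (+182 kcal, +36.4%).
- Protein: 36 versus 38 g/day, nearly equal.

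**Threshold.** A full course is 14 doses, and 0.80 × 14 = 11.2. A complier therefore takes at least 12 doses, and a patient who takes 11 (79%) is excluded.

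**Bias under no treatment effect.** Let the risk be 72% in each arm as randomised, c the proportion compliant and r the risk in non-compliers. The risk in compliers is then

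p = (0.72 − (1 − c)·r) / c.

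Worked case with c = 75% for IMN, 90% for control, and r = 84% in both:
- IMN: (0.72 − 0.25 × 0.84)/0.75 = 0.510/0.75 = 68.0%
- Control: (0.72 − 0.10 × 0.84)/0.90 = 0.636/0.90 = 70.7%
- Difference: −2.7 points, while the ITT difference is 0.

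| Compliance, IMN / control | Non-complier risk, IMN / control | Complier risk, IMN / control | Spurious difference (points) |
|---|---|---|---|
| 90% / 90% | 85% / 85% | 70.6% / 70.6% | 0 |
| 85% / 95% | 84% / 84% | 69.9% / 71.4% | −1.5 |
| 80% / 90% | 85% / 85% | 68.8% / 70.6% | −1.8 |
| 75% / 90% | 84% / 84% | 68.0% / 70.7% | −2.7 |
| 70% / 90% | 84% / 84% | 66.9% / 70.7% | −3.8 |
| 70% / 90% | 85% / 85% | 66.4% / 70.6% | −4.1 |
| 90% / 70% | 85% / 85% | 70.6% / 66.4% | +4.1 |
| 80% / 80% | 90% / 72% | 67.5% / 72.0% | −4.5 |
| 70% / 90% | 90% / 72% | 64.3% / 72.0% | −7.7 |

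The 80% / 80% row shows that equal compliance is not enough. The link between non-compliance and risk must also be the same in both arms.

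**Effect on error rate.** With 130 patients per arm before exclusions and a normal approximation, the chance of a nominally significant per-protocol result under no effect is:
- 5.0% in the first row
- 6.0% at 80% / 90% with r = 85%
- 9.7% at 70% / 90% with r = 85%
- 10.9% in the 80% / 80% row
- 22.0% in the last row

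**Scale.** In the worked case the standard error is √(0.68·0.32/97.5 + 0.707·0.293/117) ≈ 6.3 points, a 95% half-width of about 12.4. The 2.7-point bias is about 0.4 standard errors.

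**The case against.** The case against is substantial. Every per-protocol analysis loses the protection of randomisation, and this plan already ranks ITT first. Labelling and covariate adjustment of an additional analysis could well be in an unseen SAP. Section 2.5 compares compliance and tolerability between arms, so readers will be able to see differential exclusion. Section 2.4 gives counselling and a leaflet to both arms. The illustrated bias rests on assumed inputs, is usually well under one standard error, and does not reach the planned 17 points.

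Most of this stands, and it keeps the point small. It does not remove it: the article itself specifies the contrast, for the primary endpoint, and better use of baseline data already collected is available.

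Several stronger readings are tempting but unsupported:
- **That patients are removed differently by arm.** No compliance by arm is given. Listing compliance and tolerability as outcomes does not mean a difference is expected.
- **That early stoppers are excluded.** The criterion is the 80% threshold. Scattered missed doses can exclude a patient, and stopping after 12 of 14 doses does not.
- **That the protocol ties appetite or gastrointestinal symptoms to complications.** The Introduction ties only skeletal muscle loss to postoperative complications, and notes that conclusive data are lacking. It links nutritional status to mortality and survival. That non-compliers carry higher risk is therefore an assumption.
- **That patients who take the other product are mishandled.** The article describes no route by which this would happen, and its handling is ordinary SAP detail.
- **That a complier average causal effect is required.** Its exclusion restriction is doubtful here: a patient below the threshold may have taken up to 11 of 14 IMN doses, and the control is itself an active supplement.

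**Conclusion.** This is a minor but real weakness in an additional analysis. The complier contrast specified in Section 2.7.2 conditions on a post-randomisation variable, for products that differ in volume, energy and content, with no adjustment described. Under no true effect, the assumed scenarios give a spurious difference of about 1.5 to 8 points in either direction. The upper part of that range needs a link between non-compliance and risk that differs by arm. The bias is zero if compliance and that link are equal in both arms. These sizes rest on assumed compliance rates and assumed non-complier risks of 84% to 90%, with 72% in one arm where the link differs; the documents supply neither.

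A reader might infer that the trial's primary conclusion is compromised. It is not, because ITT is the main analysis and is unaffected. What is at risk is the interpretation of a per-protocol result that departs from it.

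**What to change.** Keep ITT as the basis for conclusions and amend the per-protocol paragraph as follows:
- Adjust the per-protocol risk difference for baseline NRS-2002, age, BMI and diabetes. Use regression, or standardisation or weighting if the identity-link binomial model does not converge with covariates.
- Report, by arm, the number excluded for falling below 80% and the baseline characteristics of those included and excluded.
- Label the result as supportive and not protected by randomisation.

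The four covariates come from the screening data in Section 2.6 and already define the subgroups in Section 2.5, so no new data are needed. The cost is slightly more analysis work and a few added sentences, best settled before results are seen. Adjustment will reduce the bias only as far as these covariates predict both compliance and complications; unmeasured confounding will remain. A complier average causal effect need not be required.

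### Where the trial does correct a family of secondary tests, Holm's step-down procedure would serve at least as well as the Bonferroni correction named, for a modest gain in power

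*Protocol article*

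**What the plan says.** Section 2.7.2 (Planned Analyses) of the protocol article fixes the two-sided type I error at 5%, "adjusting for Bonferroni’s correction when necessary". That clause is all it says on multiplicity. It defines no family, gives no number of tests, and does not say which objectives are adjusted.

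Some objectives clearly contain several tests. In section 2.5 the biochemical objective (no. 8) covers "changes in haemoglobin, lymphocytes, albumin, prealbumin, C-reactive protein, cholinesterase, total cholesterol, glucose, and creatinine": nine markers, followed over three time points (preadmission, day before surgery, discharge). Section 2.7.2 assigns objectives 6 to 8 to the Mann–Whitney U test. For objective 15 it says "Effect modification by subgroup will be assessed by introducing the interaction of subgroup and treatment"; section 2.5 lists four subgroup factors and two endpoints for this objective. No adjustment is attached to any of these objectives by name.

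The sample size in section 2.7.1 rests on the primary endpoint alone, at "80% power, and a two-sided type I error = 0.05".

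**The concern.** For testing hypotheses at a fixed family-wise error, Holm's procedure dominates Bonferroni. Both need no assumption about how the tests depend on each other, and both hold the family-wise error at 5%. Holm rejects every hypothesis that Bonferroni rejects, and sometimes more. A plan that names Bonferroni as its only correction therefore gives up some power wherever the correction is used.

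What is at stake is limited to lower-ranked secondary questions. If the laboratory markers are corrected as a family and several of them truly move, Bonferroni will miss a few that Holm would have declared at the same error rate.

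**Working it through.** **1. The plan's own figure.** Inputs from section 2.7.1: 72% vs 55%, two-sided 0.05, 80% power. The mean rate is 0.635.

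n per group = [1.960·√(2·0.635·0.365) + 0.8416·√(0.72·0.28 + 0.55·0.45)]² / 0.17² = (1.334 + 0.564)² / 0.0289 ≈ 124.7, so 125. This matches "a minimum 125-patient sample size was required in each group". The calculation uses unadjusted alpha, so the choice between Bonferroni and Holm does not touch it.

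**2. The two rules, for m tests at 0.05.**
- Bonferroni: reject each hypothesis with p ≤ 0.05/m.
- Holm: order the p-values. Compare the smallest with 0.05/m, the next with 0.05/(m−1), and so on, and stop at the first failure.

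The first step is the same, so the chance of at least one rejection is the same. Later thresholds are looser, so Holm never rejects less.

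**3. Assumptions not in the document.** The article gives no effect sizes for the secondary endpoints. I assume that each real effect has 80% power at unadjusted two-sided 0.05, a non-centrality of 1.960 + 0.842 = 2.802. Family sizes are also assumptions: 9 is the number of laboratory markers; 18 is 9 markers × 2 consecutive changes, a reading of the three time points and not a stated count.

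**4. Bonferroni power in closed form.**
- m = 9: alpha 0.05/9 = 0.00556, z = 2.773, power Φ(2.802 − 2.773) = 51%.
- m = 18: alpha 0.05/18 = 0.00278, z = 2.991, power Φ(2.802 − 2.991) = 42.5%.

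**5. Bonferroni against Holm by simulation** (100,000 draws of normal test statistics, independent tests; average power per real effect):

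| Family | Real effects | Bonferroni | Holm |
|---|---|---|---|
| 9 | 4 | 51% | 54% |
| 9 | 6 | 51% | 56% |
| 9 | 9 | 51% | 62–63% |
| 18 | 3 | 42.4% | 43.0% |
| 18 | 6 | 42.4% | 44.1% |
| 18 | 9 | 42.4% | 45.2% |

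Correlation of 0.4 between tests changes these figures very little. The chance of finding all six of six real effects in a family of nine is 2% vs 6% with independent tests, and 12% vs 20% at correlation 0.4. The chance of at least one rejection is identical under the two methods in every run. The chance of any false rejection stays below 5% under both.

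**6. A different effect assumption.** With 125 per arm and a standardised effect of 0.4 (normal approximation, family of 18, independent tests), the results are 56.9% vs 57.7% with 3 real, 56.8% vs 59.1% with 6, 56.8% vs 60.7% with 9, and 56.7% vs 70.4% if all 18 are real. The direction and rough size agree with step 5.

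**7. The interaction tests.** Assume equal-sized subgroups and an interaction as large as the 17-point main effect. The standard error doubles, so the non-centrality is about 2.80/2 = 1.40. With 4 factors × 2 endpoints = 8 tests, z = 2.734 and Bonferroni power is Φ(1.40 − 2.734) = 9.1%. Holm gives 9.2% with two real interactions and 9.4% with four.

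**The case against.** The strongest reply is that nothing here is wrong. Bonferroni is valid and gives strong family-wise control, and choosing it over a somewhat more powerful valid method can be called a preference. That it is valid stands. But at a fixed family-wise level Holm rejects everything that Bonferroni does, so for testing there is no trade in the error bound, and the change costs a few words.

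A reader might infer that the trial will lose power on 18 laboratory comparisons. The document does not support that. It never states 18 tests, and its conditional clause attaches no adjustment to objectives 6 to 8 or 15. If they are tested unadjusted, no power is lost. Which tests are adjusted may be set out in the full protocol or SAP, which are not shown.

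A reader might also infer that Bonferroni buys nothing. That goes too far. It bounds the expected number of false rejections, gives simple simultaneous intervals, and makes fewer false rejections when some effects are real (2.4% vs 3.6% with 9 of 18 real at standardised effect 0.4; both below 5%).

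Finally, requiring Holm for objectives 6, 7, 8 and 15 would not be a like-for-like swap. It could lower power where no adjustment was planned, and it would drop the correction for other families, such as the paired 30- and 90-day endpoints. This objection stands and limits the fix.

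**Conclusion.** The point holds as a conditional and minor one: in any secondary family that the trial corrects, Holm does at least as well as Bonferroni at the same 5% family-wise error.

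The size depends on how many effects are real and on the assumed 80% unadjusted power for each, which the article does not claim for any secondary endpoint. The gain is about 3 to 5 points in a family of nine with four to six real effects, about 11 points if all nine are real, and under 1 to 3 points in a family of 18 with up to half real. It is negligible for the interaction tests. There is none for the chance of at least one rejection or for any unadjusted test. The primary analysis and the 130 per group are not affected. The plan is not invalid as it stands.

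**What to change.** In section 2.7.2, and in the SAP, replace "adjusting for Bonferroni’s correction when necessary" with: *adjusting with Holm's step-down procedure when necessary*. Leave the choice of which tests are adjusted as the trial has it. Do not use this edit to make adjustment compulsory for particular objectives or to remove it from others.

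The cost is a few words before analysis, with no change to sample size, data collection or the primary analysis. The one small downside is that Holm has no simple matching simultaneous intervals. Report ordinary 95% confidence intervals beside the Holm-adjusted p-values, and say that the intervals are not adjusted.

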## 2. Materials and Methods

### 2.1. Study Design and Setting

This is a controlled, randomised, open-label, parallel-group clinical trial to evaluate the effect of preoperative IMN on postoperative outcomes after RC for BC.

A 7-day preoperative treatment with IMN (cases) will be compared with a 7-day preoperative treatment with standard high-calorie high-protein ONS (controls).

Informed consent will be obtained from each patient. Patients will have the right to withdraw their consent at any time without altering their current treatment.

This study will be conducted in two tertiary hospitals: (1) the Fondazione IRCCS Policlinico San Matteo, Pavia, Italy; (2) the IRCCS Ospedale San Raffaele, Milan, Italy.

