### 2.3. Recruitment and Randomization of Study Participants

Participants will be recruited during the pre-admission dietary visit, 2–3 weeks prior to surgery. The screening procedure will only require routine/daily practice examinations to check that the patient meets the inclusion and exclusion criteria. In particular, screening for inclusion and exclusion criteria will be based on the patient’s clinical history, home medication, routine pre-admission laboratory tests, dietary intake, and presence/absence of caregivers in the case of dependent or elderly patients. No payment or compensation will be provided to study participants. After signing the informed consent form, eligible participants will be randomised 1:1 by the treating physician to one of the two study arms according to a computer-generated random block randomisation list. Randomisation will be stratified by centre.

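### Clustering the primary analysis on centre with only two centres leaves the standard error one degree of freedom: type I error is about 30% with a normal critical value, or power is about 20% with a t(1) value

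*Protocol article*

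**What the plan says.** Section 2.7.2 of the protocol article fixes the model: "The primary objective will be analysed using a binomial regression model, with link identity". The risk difference and its 95% confidence interval come from that model, and for the variance "Huber–White robust standard errors will be used while clustering on centre to account for the lack of independence within centre". The test is two-sided at 5%, and "All statistical analyses will be performed using Stata 18". No few-cluster correction, reference distribution or centre term is mentioned.

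The same section extends this method to further endpoints, in the sentence that begins "The statistical analysis for the key secondary objective and for several other secondary objectives (no. 9, 13, and 14) will be performed in the same". Objectives 9, 13 and 14 are blood transfusion, compliance and tolerability.

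Two design facts bear on this. Section 2.1: "This study will be conducted in two tertiary hospitals". Section 2.3: "eligible participants will be randomised 1:1 by the treating physician to one of the two study arms", and "Randomisation will be stratified by centre". Both arms are therefore present in each hospital, and the unit of randomisation is the patient.

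**The concern.** A cluster-robust variance is estimated from the variation between cluster score totals, and its justification is asymptotic in the number of clusters. Here that number is two. The two totals must sum to zero, so they are equal and opposite and carry a single piece of information: how far apart the two hospitals' estimates happen to lie. Two hospitals that agree by chance produce a tiny standard error and a spuriously decisive result. Two that disagree by chance can bury a real effect.

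Clustering is also not called for by the design. Patients are randomised within centre, so centre is a stratification factor and not a cluster of randomisation.

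At stake are the p-value and confidence interval that decide the trial, and those of the key secondary endpoint and objectives 9, 13 and 14. The subgroup interactions (objective 15) inherit the problem by inference, because they are to be added to the corresponding models. The time-to-event objectives (1–5, 10–12) and the Mann–Whitney objectives (6–8) are not affected as described, since no clustering is stated for them.

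**Working it through.** **Inputs from the article.** Two centres (2.1); 1:1 individual allocation stratified by centre (2.3); 72% versus 55%, two-sided 0.05, 80% power, 125 per arm before drop-out (2.7.1); identity-link binomial model with standard errors clustered on centre (2.7.2).

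**Assumptions, not in the article.** A normal critical value of 1.96, the usual reference for a maximum-likelihood binomial model; a centre split between 50:50 and 80:20; the small-sample factor G/(G−1), where G is the number of clusters.

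**Step 1: the plan's sample size.** With the pooled-variance two-proportion formula and a mean rate of 0.635:

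n = [1.96·√(2·0.635·0.365) + 0.842·√(0.72·0.28 + 0.55·0.45)]² / 0.17² = (1.334 + 0.564)² / 0.0289 ≈ 124.7, that is 125 per arm.

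This matches the plan, with power 80.1%. The trial was therefore sized for an ordinary independent-patient comparison, which is not the test that section 2.7.2 specifies.

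**Step 2: the clustered standard error with G = 2.** Let w and 1−w be the centre shares and d₁, d₂ the centre risk differences, so that d = w·d₁ + (1−w)·d₂. The centre contributions are u₁ = w(d₁−d) = w(1−w)(d₁−d₂) and u₂ = −u₁. Then

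Var = [G/(G−1)]·(u₁² + u₂²) = 4w²(1−w)²(d₁−d₂)², so SE = 2w(1−w)·|d₁−d₂|.

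For equal centres this is |d₁−d₂|/2. A fit of the stated model to one simulated dataset agreed: clustered SE 0.0699 against |d₁−d₂|/2 = 0.0698, with a covariance matrix of rank 1.

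**Step 3: the test statistic under the null.** d/SE = Z₁ / (2√(w(1−w))·|Z₂|), with Z₁ and Z₂ independent standard normals. This is a scaled t on 1 degree of freedom, so

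P(reject at 1.96) = 1 − (2/π)·atan(1.96·2√(w(1−w))).

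At w = 0.5 it is 1 − (2/π)·atan(1.96) = 30.0%, and the nominal 95% interval covers 70.0%.

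**Step 4: simulation** (400,000 trials per setting, 125 per arm, 72% in both arms). Differences from the closed form reflect the discreteness of the counts.

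| Centre split | Type I error at 1.96, closed form | Type I error at 1.96, simulated | Type I error with t(1) value, simulated | Type I error, centre-stratified, non-clustered SE |
|---|---|---|---|---|
| 50:50 | 30.0% | 31% | 5.8% | 5.4% |
| 60:40 | 30.6% | 29% | 4.7% | 5.3% |
| 70:30 | 32.3% | 30% | 6.2% | 5.3% |
| 80:20 | 36.1% | 38% | 5.8% | 5.2% |

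Without the G/(G−1) factor the simulated error at 1.96 is 38–47%. A 20-point centre difference in baseline risk leaves it at 31%. Fitted binomial models (1,500 trials each, near-equal centres) gave 29.4% without a centre term and 31.8% with one, so adding centre to the model does not cure the fault while the clustering stays.

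**Step 5: what the standard error looks like.** The true value at 72% in both arms is √(2·0.72·0.28/125) = 0.057. The simulated clustered SE had a median of 0.040 and a 10th–90th percentile range of 0.008–0.096. At the lower end, any difference above 1.96·0.008 = 1.6 points is significant. At the upper end, the full 17-point design effect gives 0.17/0.096 = 1.77 and is not.

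**Step 6: power at 72% versus 55%.**
- Clustered SE, critical value 1.96: 81% (50:50), about 83% (70:30), 87% (80:20).
- Clustered SE, t(1) critical value 12.7: 18% (50:50), 21% (70:30), 22% (80:20).
- Centre-stratified difference, non-clustered SE: 81% (50:50 and 70:30).

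**The case against.** The strongest reply is that the article gives neither the critical value nor the split of patients between hospitals, so a flat claim of 30% type I error is conditional. That is correct. Loss of the 5% level and loss of the 80% power also do not occur together. With 1.96 the rejection rate at the design alternative stays at 81–87% and the damage is false positives and under-coverage. With the t(1) value the level is roughly kept and the damage is to power. This limits how the point should be stated, but neither reference rescues the analysis, and no split from 50:50 to 80:20 brings the error at 1.96 near 5%.

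A second reply is that the missing centre term may simply have been left to an analysis plan that is not shown. That is fair, and nothing here depends on it. The clustering itself is stated outright, and an analysis plan that followed it would carry the same fault.

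A third is that dependence within hospitals has to be handled somehow. With both arms randomised in each hospital, stratifying on or adjusting for centre does this. Two clusters cannot support an empirical estimate of between-hospital variation in any case.

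**Conclusion.** The analysis is wrong as written. If a normal critical value is used, type I error for the primary endpoint is about 29–38% for centre splits from 50:50 to 80:20. That is roughly six times the nominal 5% at an equal split, where the 95% interval covers about 70%. In the worst case simulated (80:20 with centre risks of 65% and 79%), type I error was 41% and coverage 59%. If a t(1) critical value is used, power is about 18–22% instead of 80%.

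These figures rest on 125 patients per arm, the plan's own event rates and the G/(G−1) factor; without that factor the error at 1.96 is larger. The same fault reaches the key secondary endpoint and objectives 9, 13 and 14. Because it concerns the test that decides the trial, it must be corrected before outcome data are analysed by arm.

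**What to change.** In section 2.7.2 (and in the analysis plan, if it repeats the sentence), delete the clustering on centre. State instead that the risk difference and its 95% confidence interval will take centre into account as the stratification factor, with model-based or heteroskedasticity-robust standard errors that are not clustered. A Mantel–Haenszel or centre-weighted risk difference does this. So does the planned identity-link model with centre as a fixed effect, or a logistic model with centre standardised to a risk difference. Name one of these in advance as the primary analysis.

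Apply the same wording to the key secondary endpoint, objectives 9, 13 and 14, and the binomial interaction models.

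The cost is one sentence. No extra patients or data are needed, and the existing sample size calculation then matches the analysis, with about 5% type I error and 81% power at 125 per arm.
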